3.2 Twenty-four hour Holter monitoring

Twenty-four hour Holter monitoring will be performed with time domain and frequency domain before HUTT at baseline and after 30 days treatment in all VVS patients.

Time domain parameters

1. standard deviation of NN intervals (SDNN)
2. standard deviation of all 5-min average NN intervals (SDANN)
3. square root of mean of the sum of squares of successive NN interval differences (rMSSD)
4. number of successive NN interval differing by >50ms divided by the total number of successive NN intervals (pNN50)

Frequency domain parameters

1. low frequency (LF): at frequency between 0.04--0.15 Hz
2. high frequency (HF): at frequency between 0.15--0.40 Hz
3. and the low frequency/high frequency ratio (LF/HF)

3.3Detailed procedures of the modified Valsalva manoeuver (MV)

3.3.1 Expiration strength grades and breath-hold time of the modified MV.

Expiration strength is divided into 3 grades (Grade A = 20 mm Hg, Grade B = 30 mm Hg and Grade C = 40 mm Hg). Expiration strength is controlled by blowing into a tube connected to sphygmomanometer. Breath-hold time is divided into 2 lengths (1 = 8 seconds, 2 = 15 seconds).

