**Statistical analysis**

Continuous variables will be presented as mean ± standard deviation (SD). Continuous data with normal distribution will be assessed by Student’s *t*-test or one-way ANOVA with Post Hoc test (Bonferroni) as indicated, and non-normal distribution data will be tested by two-tailed Mann–Whitney U test or Kruskal-Wallis non-parametric test as indicated for the baseline characteristics of the three groups. The Chi-square test will be used to compare the ratio or percentages of categorical variables of the three groups. The Chi-square test will be used to compare the positive rate of HUTT at baseline and after 30 days treatment between NVM and MVM groups. The incidences of recurrent syncopeduring 12 months follow-up of NVM and MVM groups will be compared by log rank test of Kaplan-Meier curve. HRV indexes among the three groups will be assessed by one-way ANOVA with Post Hoc test (Bonferroni) for normal distribution data, Kruskal-Wallis non-parametric test for non-normal distribution data. HRV indexes between baseline and after 30 days treatment will be assessed by Student’s *t*-test for normal distribution data, two-tailed Mann–Whitney U test for non-normal distribution data. The relationship between HUTT and recurrent syncope, HRV and recurrent syncope during 12 months follow-up in VVS patients will be assessed by univariable and multivariable Cox proportional hazards models after 30 days intervention. Receiver operating characteristic (ROC) curves of HRV values at 30 days after intervention will be used to predict 12 months follow-up recurrent syncope. The cutoff values of HRV will be derived from ROC curve analysis by maximizing the sum of the sensitivity and specificity. All statistical analyses will be performed with SPSS version 19.0. *P*<0.05 is considered statistically significant.

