**Expected results**

1 VVS患者存在自主神经功能失调紊乱。

The data will be similar at baseline among the three groups. Positive rate of HUTT will be lower in the MVM group than in the NVM group after 30 days treatment. The incidence of rate of recurrent syncope will be lower in the MVM group than in the NVM group during 12 months follow-up. VVS patients have autonomic nervous function imbalance by HRV analysis among the three groups and between baseline and after 30 days treatment. The underlying mechanism of MVM treating VVS is to improve autonomic nervous function.

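### HRV is linked to recurrence only through its 30-day level: valid as prognosis, but it could be misread as support for the autonomic mechanism because no named analysis ties baseline HRV or its change to recurrence

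*Protocol*

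**What the plan says.** Holter monitoring with time- and frequency-domain HRV is done "before HUTT at baseline and after 30 days treatment in all VVS patients" (Protocol, section 3.2). The Statistical analysis section then uses HRV in four ways:

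- a comparison among the three groups;
- a comparison of baseline with 30 days ("HRV indexes between baseline and after 30 days treatment will be assessed by Student"'s t-test, or Mann–Whitney);
- univariable and multivariable Cox models relating HRV to 12-month recurrence, described only as "will be assessed by univariable and multivariable Cox proportional hazards models after 30 days intervention";
- ROC analysis: "Receiver operating characteristic (ROC) curves of HRV values at 30 days after intervention will be used to predict 12 months follow-up recurrent syncope", with a cutoff chosen to maximise sensitivity plus specificity.

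The first two do not involve recurrence. The last two do. The ROC predictor is explicitly the 30-day value, and the Cox wording points the same way. The covariates of the multivariable Cox model are not listed.

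The second objective includes the potential mechanism of MVM. Expected results states "VVS patients have autonomic nervous function imbalance by HRV analysis among the three groups and between baseline and after 30 days treatment", and then "The underlying mechanism of MVM treating VVS is to improve autonomic nervous function".

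**The concern.** Improvement in autonomic function is a change within a patient. A 30-day HRV value mixes what the patient brought to the trial with whatever happened in the 30 days. If HRV is moderately stable and patients with poorer HRV faint more often, the 30-day value will be associated with recurrence even when MVM changes neither HRV nor syncope.

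The Cox and ROC analyses are the only named ones that connect HRV with the clinical outcome. A reader who wants to say that MVM prevents syncope because it improves HRV would naturally reach for them. They cannot separate HRV that improved from HRV that was always better. Nor, without a baseline curve, can they show that the second Holter predicts anything the first did not.

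**Working it through.** The Protocol gives no event rate, HRV effect or HRV correlation, so there is no figure of its own to reproduce. The check is a simulation with MVM inert, asking how often 30-day HRV is nevertheless significant.

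**From the Protocol:** 60 VVS patients, 30 per arm; 12 months' follow-up after the 30-day therapy; two-sided 0.05.

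**Assumed:** number of recurrences; hazard ratio (HR) per SD of HRV; correlation between baseline and 30-day HRV (*r*).

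Two risk models were used, with event times exponential and censored at 12 months:

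- *Measured-baseline model:* the hazard depends on the baseline HRV value as recorded, and the 30-day value has correlation *r* with it.
- *Stable-trait model:* baseline = √r·T + √(1−r)·noise and 30-day = √r·T + √(1−r)·fresh noise. The hazard depends on the trait T.

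**Measured-baseline model** (2,500 trials per setting, about 22-23 events), % of trials significant:

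| HR per SD | r | 30-day alone | change alone |
|---|---|---|---|
| 1.5 | 0.5 | 14 | 16 |
| 1.5 | 0.7 | 27 | 11 |
| 1.5 | 0.85 | 38 | 8 |
| 2 | 0.5 | 31 | 31 |
| 2 | 0.7 | 54 | 20 |
| 2 | 0.85 | 72 | 12 |

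A separate run of 1,500 trials gave 16-36% (HR 1.5) and 33-76% (HR 2) for the 30-day value alone. With baseline and arm added, the rate for the 30-day value was 5-7% across runs.

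**Stable-trait model** (1,500 trials per setting; 12-month recurrence 30% or 50%, that is about 60 × 0.30 = 18 or 60 × 0.50 = 30 events), % of trials significant. The last column is the test of arm on 30-day HRV adjusted for baseline (ANCOVA):

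| Recurrence | r | HR | 30-day alone | 30-day + arm | 30-day + baseline | change alone | ANCOVA, arm |
|---|---|---|---|---|---|---|---|
| 30% | 0.5 | 1.5 | 23.3 | 23.1 | 11.5 | 4.9 | 4.8 |
| 30% | 0.5 | 2 | 52.5 | 52.3 | 22.1 | 4.3 | 4.1 |
| 30% | 0.7 | 1.5 | 29.3 | 29.1 | 8.6 | 5.5 | 5.1 |
| 30% | 0.7 | 2 | 67.2 | 66.3 | 18.5 | 6.1 | 4.3 |
| 30% | 0.9 | 1.5 | 35.4 | 34.5 | 7.1 | 5.9 | 5.5 |
| 30% | 0.9 | 2 | 80.7 | 80.1 | 10.1 | 5.0 | 5.0 |
| 50% | 0.5 | 1.5 | 31.7 | 31.9 | 14.1 | 4.4 | 5.1 |
| 50% | 0.5 | 2 | 69.4 | 68.7 | 32.2 | 4.9 | 4.9 |
| 50% | 0.7 | 1.5 | 43.6 | 43.7 | 12.4 | 4.6 | 5.3 |
| 50% | 0.7 | 2 | 83.2 | 83.1 | 26.6 | 5.9 | 5.8 |
| 50% | 0.9 | 1.5 | 54.9 | 54.9 | 7.9 | 5.7 | 5.1 |
| 50% | 0.9 | 2 | 92.5 | 91.9 | 13.3 | 5.2 | 5.5 |

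With HR 1.0 (no trait effect) the 30-day value alone is significant in 5.1-6.8%, so the test itself behaves. In the settings tabulated, mean ROC area for 30-day HRV was 0.60-0.73.

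At about 22-23 events and r 0.5-0.85, the two models together put the 30-day value alone at roughly 16-86%. Under the stable trait, baseline plus arm left 13, 11 and 9% (HR 1.5; r 0.5, 0.7, 0.85) and 25, 21 and 13% (HR 2); repeated runs span about 8-26%.

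Three things follow.

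1. Adding arm alone does nothing, so this is separate from leaving treatment out of the model.
2. Adding baseline helps greatly. It is complete only if recorded baseline is what drives risk. If a trait measured with noise drives it, the 30-day value is a second reading of the same trait and keeps some signal.
3. Change can replace the 30-day value only if baseline stays in the model: β₁·D30 + β₂·B = β₁·(D30 − B) + (β₁ + β₂)·B, so β₁ is the same coefficient. Change alone holds its level under the stable trait (4-6%) but not under the measured-baseline model (8-31% above).

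**The case against.** Four objections have force.

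*The plan does not assign the mechanism to these analyses.* The Statistical analysis section speaks of a relationship and of prediction. Expected results cites the three-group and baseline-to-30-day comparisons for autonomic imbalance, then states the mechanism without citing Cox or ROC. A reader might infer that the plan intends these analyses as proof of mechanism; the text does not say so. This stands: the association could be misread, and no more can be claimed.

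*Prediction from a 30-day value is legitimate.* The value is taken where the 12-month follow-up starts. This stands too: as prognosis, nothing is wrong. What is missing is a statement that the results are limited to prognosis.

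*The multivariable covariates are open.* A reader might infer that baseline HRV is ignored. It is used in the baseline-to-30-day comparison, and an SAP not shown here may enter it in the multivariable Cox model. This stands for that model only. The univariable Cox has no second term, and the ROC predictor is fixed: "curves of HRV values at 30 days after intervention will be used to predict 12 months follow-up recurrent syncope".

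*The percentages are assumed.* Correlation, hazard ratio and event count come from no document. This stands. The range shows that the effect can be large, not how large it will be here.

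**Conclusion.** The point holds in a limited form. The plan links HRV to recurrence through the 30-day level, explicitly for the ROC and by wording for the Cox, although a baseline value exists for every VVS patient. Such an association is valid as prognosis. It does not support the mechanism in Expected results, because a pre-existing trait would produce it in roughly 16-86% of trials with MVM inert. That range rests on 60 patients, about 22-23 events, HR 1.5-2 per SD and correlation 0.5-0.85, all assumed except the sample size.

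It would be tempting to conclude that adjusting for baseline HRV settles the mechanism. It does not: about 5-7% false positives remain if recorded baseline drives risk, and about 8-26% if a noisily measured stable trait does. Even a sound patient-level coefficient is observational and does not attribute the HRV change to MVM.

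This is a secondary analysis serving a stated objective. The point warrants a change of wording and does not touch the recurrence or HUTT comparisons.

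**What to change.** In the Statistical analysis section:

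- (a) State that Cox and ROC results on 30-day HRV alone are prognostic and are not evidence of mechanism.
- (b) Add, one HRV index at a time, a Cox model with the 30-day value, the same patient's baseline value and arm (or change, with baseline kept in the model). Show the baseline-HRV ROC curve beside the 30-day curve, and claim value for the second Holter only for its gain over baseline.
- (c) Rest any statement that MVM improves autonomic function on the MVM-versus-NVM difference in 30-day HRV adjusted for baseline HRV, which kept a 4-6% false-positive rate in the simulation. Treat the Cox coefficient given baseline as supportive only.

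The 4-6% assumes that all 60 randomised patients are analysed. The exclusion of MVM patients who do not reach the top level within 10 days (section 3.3.2.2) is a separate threat to that comparison.

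Cost: wording and a little analysis on data already to be collected. The extra terms widen the intervals, and the mechanism result will probably look less favourable.

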**The safety and efficacy of modified step-up graded Valsalva manoeuver in patients with vasovagal syncope**

**(Version 1.0 August 20, 2012)**

**Department of Cardiology Puai Hospital**

**Abstract**

Therapeutic options for vasovagal syncope (VVS) remain challenging now. Non-pharmacological therapies, especially the physical maneuvers, are viewed as important and promising strategies for reducing the syncope recurrences. We will plan to recruit 60 VVS patients with syncope history and positive head-up tilt table testing (HUTT). They will be randomly divided into conventional treatment group (NVM group, n=30) and conventional treatment plus standard MVM for 30 days group (MVM group, n=30). The rate of positive HUTT after 30 days treatment and incidence of recurrent syncope during 12 months follow-up will be observed between the two groups. Heart rate variability (HRV) indexes among the three groups and between baseline and after 30 days treatment will be analyzed. The safety and efficacy of the modified Valsalva maneuver (MVM) in VVS patients will be observed. We attempt to find out a new way to treat VVS and discovery the pathogenesis of VVS and the potential mechanism of MVM in VVS.

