**Methods**

1. Study population

Inclusion criteria: we will recruit VVS patients aged between 18 to 80 years old with at least three lifetime syncopal spells associated with positive head-up tilt testing.

Exclusion criteria: Patients will be excluded if they have other causes of syncope, cannot give informed consent, have serious diseases or psychopath. Women who are pregnant, ready to pregnant, or breast-feeding a baby will be excluded.

2. Divided groups

VVS patients will be randomly divided into two groups: NVM group and MVM group, each 30 patients. Healthy control group (CON group) is 30 patients.

2.1 NVM group: Conventional therapy included: 1) Patient education for the importance of taking enough dietary salt and fluid in daily life. 2) Avoid medications such as diuretics and vasodilators.

2.2 MVM group: conventional treatment plus standard MVM for 50-60 minutes once a day for 30 days.

2.3 CON group: Age and gender matched healthy volunteers without syncope will be enrolled as healthy controls.

3. Study methods

All patients will give informed consent for participation in the study. Age, gender, body mass index, heart rate, blood pressure and biochemical indexes will be record at baseline in the three groups. Frequency and duration of syncope, syncope-induced trauma as well as disease history and current medications will be record in VVS patients.

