3.3.2.2 Accommodation phase

The MV maneuvers will be performed in the morning session consisted 8 VM and in the afternoon session consisted 7 VM. Patients will be asked to perform VM from A1 level to C2 level gradually. Patients who do not reach the C2 level within 10 days will be excluded from the study.

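### HRV cut-offs tuned by maximising sensitivity plus specificity can only be judged in the same 60 or fewer patients, so their apparent accuracy is too high on average

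*Protocol*

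**What the plan says.** Protocol, Statistical analysis, states the purpose: "Receiver operating characteristic (ROC) curves of HRV values at 30 days after intervention will be used to predict 12 months follow-up recurrent syncope". The next sentence states the rule: "The cutoff values of HRV will be derived from ROC curve analysis by maximizing the sum of the sensitivity and specificity". The section closes with one general significance criterion, P "<0.05 is considered statistically significant", and no adjustment across HRV indices.

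Methods, 3.2, lists four time-domain indices (SDNN, SDANN, rMSSD, pNN50) and three frequency-domain indices (LF, HF, LF/HF), seven in all. No index is named as the predictor, and neither a threshold nor a direction of the association is set in advance.

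On the sample, Methods, section 2, says: "VVS patients will be randomly divided into two groups: NVM group and MVM group, each 30 patients". Section 3.3.2.2 may reduce that number: "Patients who do not reach the C2 level within 10 days will be excluded from the study". Healthy controls have Holter recordings, but section 3.4 follows only the syncope patients for recurrence. No second sample is planned.

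**The concern.** A cut-off chosen to make sensitivity plus specificity as large as possible in a sample fits that sample's chance pattern as well as any real signal. Reading its accuracy in the same patients then gives an optimistic answer. The optimism is larger in small samples, larger again if the best of several indices is highlighted, and larger still if the data also decide whether high or low values count as positive.

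Mechanism is one of the two stated objectives, and a published HRV threshold may be applied to other patients. If its accuracy is overstated, a weak marker looks useful and a useless one looks weakly informative.

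**Working it through.** **Plan's own figure.** The protocol gives no expected AUC, cut-off, accuracy or number of recurrences for this analysis, so there is nothing to reproduce.

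**Inputs from the protocol.** n = 60 at most; 7 indices; cut-off at the maximum of sensitivity + specificity.

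**Assumptions.** 20 recurrences among 60 (15 and 25 also tried); normally distributed indices; pairwise correlation between indices 0.3 to 0.8; nobody lost before 12 months.

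**Measure.** Youden index J = sensitivity + specificity - 1. A useless index has true J = 0 at every cut-off.

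**Step 1: useless indices.** In each simulated trial the cut-off was chosen by maximum J and the apparent J recorded. Means:

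| Recurrences of 60 | ROC direction | One index | Best of seven |
|---|---|---|---|
| 20 | fixed in advance | 0.15 to 0.16 | 0.23 to 0.27 |
| 20 | chosen from the data | 0.22 | 0.30 to 0.33 |
| 15 to 25 | fixed in advance | 0.15 to 0.17 | 0.22 to 0.29 |
| 15 to 25 | chosen from the data | 0.21 to 0.24 | 0.29 to 0.35 |

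The best-of-seven column applies only if the most favourable index is the one emphasised.

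**Step 2: a weak real marker.** For AUC 0.65 with equal-variance normal values, the shift is d = √2 × Φ⁻¹(0.65) = 1.414 × 0.385 = 0.545 SD. The best J that any cut-off can deliver is 2Φ(d/2) - 1 = 2Φ(0.272) - 1 = 0.21. With 20 recurrences among 60 and one index, the mean apparent J is 0.33, and the mean true J at the chosen cut-off is about 0.19. The average overstatement is 0.33 - 0.19 = 0.14, and 0.33/0.19 = 1.7 times the true value. In about 7% of runs with the direction fixed in advance, the apparent J was at or below the true J.

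**Step 3: the AUC test, which needs no cut-off.** For one useless index the false-positive rate stays near 5%. For at least one of seven it is 1 - 0.95⁷ = 30.2% if they are independent, and 14% to 31% in simulation (correlation 0 to 0.8, 50 or 60 patients).

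**Step 4: treatment arm.** Expected results anticipates that MVM lowers recurrence and works by improving autonomic function. As an illustration with assumed figures, take recurrence of 50% in NVM and 20% in MVM, a 1 SD difference in HRV between arms, and no link between HRV and recurrence within arms. With equal arms, a patient with recurrence is from NVM with probability 0.5/0.7 = 0.714, and one without with probability 0.5/1.3 = 0.385. The AUC between arms is Φ(1/√2) = 0.76. Pooled AUC = 0.714 × 0.615 × 0.76 + 0.286 × 0.385 × 0.24 + 0.45 × 0.5 = 0.33 + 0.03 + 0.23 = 0.59. HRV would appear to predict recurrence only because it reflects the assigned arm.

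**The case against.** Maximising sensitivity plus specificity is a standard, openly stated rule, and internal validation, intervals and arm adjustment are details that a SAP often holds. The SAP has not been seen and may supply them. That limits the point, but the protocol itself fixes a data-driven threshold for a predictive purpose with no other sample planned. Followed as written, the rule gives biased accuracy.

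The objection rightly rules out several stronger readings:

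- **That the accuracy is bound to be too high, or that the cut-offs must fail in new patients.** The optimism is an average. Some trials would show none, and in the AUC 0.65 example the cut-off still delivers about 0.19.
- **That useless HRV values would almost certainly reach significance.** If patients were split at the chosen cut-off and compared by an uncorrected chi-square test, with direction also chosen from the data, at least one of seven useless indices would reach P<0.05 in 84% to 97% of simulated trials of 60. The protocol states no such test. A significant AUC is much less likely (Step 3), and a J of 0.22 is poor accuracy that few would call predictive.
- **That the ROC analysis pools the arms.** The Cox sentence refers to the syncope patients as a whole; the ROC sentence names no population.
- **That patients lost early are misclassified.** With a fixed one-year follow-up and no loss, everyone's status is known. The protocol gives no loss figure, and the companion Cox models of HRV and recurrence handle censoring.

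The upper figures in Step 1 also depend on choices that the protocol leaves open: the direction, and whether one winning index is highlighted.

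**Conclusion.** The point holds in a limited form. The rule gives upward-biased sensitivity and specificity, because no patients other than the 60 or fewer who generate the cut-offs are available to judge them. Under the stated assumptions, the average excess in J for a useless index is about 0.15 to 0.22, or 0.23 to 0.33 if the best of seven is highlighted; for a marker with an AUC of 0.65 it is about 0.14. The size rests on an assumed recurrence count and correlation. The direction of the bias does not, and a sample reduced by the C2 exclusion would increase it.

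The arm and censoring questions are conditional: the first matters if treatment shifts both HRV and recurrence, as the protocol expects, and the second only if patients are lost before 12 months. The change is worth making, but for a secondary, mechanistic analysis.

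**What to change.** - Report AUC, sensitivity and specificity for each index with 95% confidence intervals, corrected for optimism by a bootstrap. Each resample should repeat the choice of cut-off, and of index and direction where these are taken from the data. Naming one index and its direction in advance would remove those two sources.
- Label any cut-off exploratory.
- If patients are lost before 12 months, use a time-dependent ROC that allows for censoring, consistent with the log-rank and Cox analyses.
- Show the HRV results by arm or adjusted for arm.

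No extra patients, visits or measurements are needed. The cost is a little more analysis work, partly outside SPSS, and less favourable accuracy figures.

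### Neither efficacy outcome, tilt-test positivity at 30 days or recurrent syncope over 12 months, is named primary, and each is judged at P<0.05, so efficacy could be claimed on whichever succeeds

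*Protocol*

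**What the plan says.** The Objective section speaks of safety and efficacy in general and names no outcome. The Abstract puts two outcomes side by side: "The rate of positive HUTT after 30 days treatment and incidence of recurrent syncope during 12 months follow-up will be observed between the two groups".

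Statistical analysis gives each its own comparison of the randomised groups. For the tilt test: "The Chi-square test will be used to compare the positive rate of HUTT at baseline and after 30 days treatment between NVM and MVM groups". For syncope, the 12-month incidences "of NVM and MVM groups will be compared by log rank test of Kaplan-Meier curve". Expected results predicts a lower rate in the MVM group for both and ranks neither.

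The only threshold is the closing one: "P*<0.05 is considered statistically significant". The only multiplicity adjustment is the Bonferroni post hoc step after ANOVA, which handles pairs of groups within one variable and does not reach across outcomes.

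**The concern.** The two outcomes are not interchangeable. HUTT positivity is a laboratory response at 30 days; recurrent syncope is what the patient lives with over the following year. Statistical analysis itself plans Cox models to relate HUTT to later recurrence, so the protocol treats the link between them as a question to be answered.

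With 30 patients per arm the two tests may well disagree. If HUTT improved significantly and recurrence did not, the protocol would give no basis for saying whether the trial had succeeded. The choice could then be made with the results in view, which gives a useless treatment two chances to look effective. Detailed multiplicity procedures may sit in a statistical analysis plan that is not at hand, but naming the primary outcome is a matter for the protocol.

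**Working it through.** The protocol states no familywise error rate, so there is no figure of its own to reproduce.

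**Inputs from the protocol**
- Two efficacy tests of MVM against NVM: chi-square on HUTT at 30 days, and log-rank on recurrence. The baseline HUTT comparison is not counted, because a positive HUTT is an inclusion criterion.
- 0.05 for each test (Statistical analysis).
- 30 patients per randomised arm (Methods, Divided groups).

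**Assumptions**
- Both tests are two-sided. The protocol says so only for the rank test ("two-tailed Mann–Whitney U test for non-normal distribution data").
- The correlation between the two test statistics is not given, so a range is shown.

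**At least one P<0.05 in either direction, no true effect**

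Independent: 1 − (1 − 0.05)² = 1 − 0.9025 = 0.0975, or 9.75%.

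**At least one significant result favouring MVM, no true effect**

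A two-sided 5% test puts 2.5% in each direction. Independent: 1 − (1 − 0.025)² = 1 − 0.950625 = 0.0494, or 4.9%, against 2.5% for one test.

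**With correlation** (400,000 draws from a bivariate normal distribution)

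| Assumed correlation | Either direction | Favouring MVM only |
|---|---|---|
| 0 (formula) | 9.75% | 4.9% |
| 0.3 | 9.5% | 4.7% |
| 0.5 | 9.1% | 4.5% |
| 0.7 | 8.4% | 4.2% |
| 0.9 | 7.1% | 3.5% |

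**Does the small sample make the tests conservative enough to absorb this?** For the chi-square test, no. The exact size of the uncorrected test at 30 against 30 is 4.9%, 5.2%, 4.9% and 4.9% at null positive rates of 0.3, 0.5, 0.7 and 0.8.

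**After a fix**
- One primary at 0.05, with the second outcome tested only if the first is significant: at most 5%.
- Either may suffice, at 0.025 each: 1 − 0.975² = 4.94% if independent, and at most 5% in any case.

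**The case against.** Three objections deserve weight.

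First, the sentence on P<0.05 defines statistical significance; it does not say that one significant outcome proves efficacy. That is right. A reader might infer that the protocol prescribes an either-suffices rule, but no success rule is written at all. The weakness is that the choice is left open.

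Second, the expected effects are directional, so a false claim that MVM works needs a significant result in its favour. That also stands. On this count the error is 3.5% to 4.9%. It is up to about double the 2.5% of a single test, but it does not exceed 5%.

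Third, a reader might infer that HRV makes matters far worse. There are seven indices, four in the time domain (from "standard deviation of NN intervals (SDNN" onward) and three in the frequency domain (ending "and the low frequency/high frequency ratio (LF/HF"), and Statistical analysis compares them among groups and before against after. It is tempting to add these to the count, or to multiply indices by comparisons into dozens of tests. The documents do not support that for the efficacy claim:
- The second objective and Expected results use HRV for pathogenesis and mechanism: "VVS patients have autonomic nervous function imbalance by HRV analysis among the three groups and between baseline and after 30 days treatment".
- The three-group test includes healthy controls, where a real difference is expected, so its null is not a null about MVM.
- Statistical analysis does not list how many HRV tests will be run. They could not be independent in any case, since LF/HF is built from LF and HF and the comparisons share recordings.
- Handling multiplicity across such indices may properly be left to the statistical analysis plan.

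**Conclusion.** The point holds for the two efficacy outcomes only. Without a ranking, the chance of at least one false positive is 9.75% under independence and about 7% to 9.5% at correlations of 0.9 to 0.3. In MVM's favour alone it is about 3.5% to 4.9%, against 2.5%.

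The correlations are assumptions. The outcomes come from the same patients, so independence is the ceiling here and not the expected case. A reader might infer that the risk of wrongly declaring MVM effective is far above 5%; the directional figures do not bear that out. The inflation is moderate. The more practical harm is that the trial's main conclusion is not fixed before the results are known.

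**What to change.** In Statistical analysis, and in the Abstract to match, before any outcome comparison is made:

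1. Name time to first recurrent syncope over the 12-month follow-up as the primary outcome, MVM against NVM, by log-rank at two-sided 0.05. The Abstract and Background present treatment as a way to reduce recurrences, so this outcome matches the purpose of the trial.
2. Make HUTT positivity at 30 days secondary, by chi-square at two-sided 0.05, confirmatory only if the primary is significant.
3. Label the seven HRV indices exploratory, as evidence on mechanism.

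If the sponsor wants either outcome to suffice, test each at 0.025 and say so.

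The cost of ranking is that a significant HUTT result alone would no longer establish efficacy. There is no delay, since the Study plan places analysis after follow-up.

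Splitting alpha costs power. For two proportions with 30 per arm, assumed rates of 70% against 40% give about 65% power at 0.05 and 54% at 0.025; 80% against 40% give about 91% and 84%. These rates are illustrative. The protocol gives no event rates or power calculation, so whether 30 per arm can support recurrence as the sole primary cannot be checked, and the sponsor should state the basis when naming it.
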